## Abstract

**Introduction:**

We describe the protocol for a project that will use linkage of routinely collected NHS data to answer a question about the nature and effectiveness of liaison psychiatry services in acute hospitals in England.

**Methods and analysis:**

The project will use three data sources: (1) Hospital Episode Statistics (HES), a database controlled by NHS Digital that contains patient data relating to emergency department (ED), inpatient and outpatient episodes at hospitals in England; (2) ResearchOne, a research database controlled by The Phoenix Partnership (TPP) that contains patient data relating to primary care provided by organisations using the SystmOne clinical information system and (3) clinical databases controlled by mental health trusts that contain patient data relating to care provided by liaison psychiatry services. We will link patient data from these sources to construct care pathways for patients who have been admitted to a particular hospital and determine those patients who have been seen by a liaison psychiatry service during their admission.

Patient care pathways will form the basis of a matched cohort design to test the effectiveness of liaison intervention. We will combine healthcare utilisation within care pathways using cost figures from national databases. We will compare the cost of each care pathway and the impact of a broad set of health-related outcomes to obtain preliminary estimates of cost-effectiveness for liaison psychiatry services. We will carry out an exploratory incremental cost-effectiveness analysis from a whole system perspective.

**Ethics and dissemination:**

Individual patient consent will not be feasible for this study. Favourable ethical opinion has been obtained from the NHS Research Ethics Committee (North of Scotland) (REF: 16/NS/0025) for Work Stream 2 (phase 1) of the Liaison psychiatry—measurement and evaluation of service types, referral patterns and outcomes study. The Confidentiality Advisory Group at the Health Research Authority determined that Section 251 approval under Regulation 5 of the Health Service (Control of Patient Information) Regulations 2002 was not required for the study ‘on the basis that there is no disclosure of patient identifiable data without consent’ (REF: 16/CAG/0037).

Results of the study will be published in academic journals in health services research and mental health. Details of the study methodology will also be published in an academic journal. Discussion papers will be authored for health service commissioners.

Strengths and limitations of this studyStudy designs based on the linkage of routinely collected NHS data enable the generation of evidence regarding the cost-effectiveness and efficiency of health services, where alternative study designs such as randomised controlled trails or other individually consented study designs would be infeasible.While our study will evaluate the impact of acute inpatient hospital work carried out by liaison psychiatry teams and will not cover work undertaken in the emergency department, outpatient or primary care setting, the findings will be highly relevant, as previous claims for cost savings resulting from the implementation of liaison psychiatry services have been primarily based on their inpatient hospital work.Study designs based on the linkage of routinely collected NHS data present technical, ethical and legal challenges which must be considered from the start, including their implications for the validity and generalisability of insights and for project resources.

## Introduction

Liaison psychiatry services provide assessment and treatment for people with coexistent physical and mental health problems.^1–4^ Such services are provided predominantly in the acute hospital setting in the UK, although more recently services have emerged to support the management of people with complex physical and mental health problems in primary as well as secondary care.^5^ Liaison psychiatry services have the potential to improve both the quality of care and overall outcomes for people with mental and physical health problems. There is also a suggestion that liaison psychiatry services in the acute hospital setting will produce cost savings by reducing length of stay, even though it is estimated that services see a small proportion (1%–5%) of all patients admitted to acute beds.^6–12^ For these reasons, NHS England has invested in expanding liaison psychiatry services to acute hospitals.^13 14^

The research evidence has not been strong for the cost-effectiveness of liaison psychiatry *services*^15 16^ as opposed to evidence on the cost-effectiveness of some of the *individual interventions* used in those services.^17 18^ For that reason, more research is needed using robust designs derived from health services research. Claims for cost-effectiveness of liaison psychiatry go to the origins of the specialty before World War II. Individual components have been tested in randomised controlled trials (RCTs), but there have been few attempts to judge the cost-effectiveness of whole services. Although it has been argued that they can pay for themselves—the cost-offset debate of the 1980 and 1990s^19^—in truth, the cost-effectiveness evidence for any liaison psychiatry service is limited. Holmes *et al*^20^ identified only two RCTs; some smaller non-randomised studies include working age and older patients, and older and non-definitive work on cost-offsetting.

There are three main reasons why visiting the question now is timely.

First, cost pressures in the NHS and the emergence of commissioning led by Clinical Commissioning Groups will continue to lead to re-profiling of services and especially attempts to reduce unnecessary hospital costs. Work on developing and implementing risk stratification models is an illustration and it is interesting that many of these models identify comorbid physical and mental health problems as a risk, both for increased healthcare costs and for the main driver of such costs which is unscheduled hospital admission. A study from Birmingham describing the evaluation of a rapid assessment, intervention and discharge service (previously widely known by the acronym RAID) was widely promoted and is leading to commissioning of similar services that will be hoped to reduce costs.^21 22^ There were however substantial problems with that evaluation: it reported only on the first 9 months of delivery of a new service; it used a simple before and after design; it compared outcomes between referred and a matched group of non-referred patients in only 79 cases with minimal matching that cannot have dealt with indication bias and much of the benefit was attributed to the so-called indirect liaison cases who were in fact not seen by the service but assumed to benefit by its existence in the hospital. Other ‘RAID’-like services have also reported large savings in cost or reductions in hospital use following implementation.^23 24^ So a key answer to the question of why this research is needed now is the pressing need to confirm or refute the very striking claims made for similar services, but using larger numbers and more robust research methods.

Second, there is a danger of losing sight of the other main functions of liaison psychiatry services, which do not exist only to reduce costs in the general hospital but which are aimed at improving the well-being of patients, some of whom are being treated entirely or appropriately in the general hospital and happen to need mental health service input because of the complexity of their problems.

Third, and related to the second point above, service commissioning and provision will benefit from a more standardised approach to service descriptors. Without more detailed knowledge about how to define the service being commissioned and how to evaluate whether it is working to remit and to improve Health-Related Quality of Life for patients, there is a risk of enthusiastic commissioning of services that look superficially similar to each other and to a model reported as cost-effective, when in fact either at the time or over a period after commissioning there are differences in staffing or referral patterns that invalidate the original commissioning assumptions. An important function is served by studies that describe what patient groups actually receive—what sort of service and in what numbers.

This research is thus timely in exploring methods to evaluate the function and performance of liaison psychiatry services.

There are, however, challenges in conducting such research.

First, defining exposure to liaison psychiatry is difficult because there is substantial heterogeneity in the composition, purpose and size of liaison psychiatry services. For example, a recent survey conducted in England^25^ found that just over half of the services provided a 24-hour 7-day service and only one-third ran specialist outpatient clinics. Most of the services provided cover of acute hospital wards and emergency department (ED) and nearly all services were multidisciplinary, but staff mix varied such that about one-third employed less than one full-time equivalent of a consultant in psychiatry. Only one-third of services had separate teams for older adults and adults of working age. These differences were not fully explained by variation in acute hospital characteristics. Also, the mechanism by which liaison psychiatry services might produce improved patient and organisational outcomes is unclear—for example, with some suggesting that the main benefit is by securing rapid discharge to community-based services, while others emphasise the specialist nature of shared inpatient management or of outpatient clinics provided by the service.

Second, defining service outcomes is difficult because there is also substantial heterogeneity in the patient populations seen in liaison psychiatry services. For example, service outcomes (and performance indicators) will not be the same for somebody seen in the ED after an act of self-harm, an older person with postoperative agitated behaviour seen on a surgical ward or somebody with chronic unexplained pain referred from a pain clinic.

To evaluate the impact of liaison psychiatry services on the outcomes of patients in acute hospital settings, we therefore need to be able to do three things. *Patients* attending selected hospitals need to be characterised with respect to their physical and mental health. The prognosis for any given mental health problem is strongly influenced by the prior history of mental disorder, so the nature of the psychiatric problem needs to be described not just at the time of admission but in the preceding months. This longitudinal picture can only be determined reliably and for all patients in any sample by the use of routine data from primary care. Patient *healthcare contact* in both primary and secondary care services needs to be recorded. And *outcomes* need to be identified beyond the immediate spell in hospital. The heterogeneity of both patient population and service exposures requires a large study in terms of number of hospitals and patients.

In addition to these measurement problems, there is a challenge in choosing a robust research design. There have been several RCTs showing the effectiveness of individual components of liaison psychiatry services, but an individually randomised RCT of a whole service configuration would be impractical. The *heterogeneity of case mix* even in simpler services will require numbers beyond what could be reasonably recruited, and there are major challenges in obtaining a large representative sample when individual consent is required. Because many patients seen by liaison psychiatry services lack mental capacity at the time of service contact, an individually consented study is not feasible and an individually RCT study would not in any case answer the service-level question.

We also considered a cluster RCT of different liaison psychiatry services. *Heterogeneity of service provision*, as identified in our national survey of services in England, would make such a study prohibitively large.

For these reasons, our view is that a large-scale observational study based on analysis of *routinely collected NHS data* and which is not predicated on individual patient consent is the best option.

## Methods and analysis

### Study design

Retrospective cohort design, comparing outcomes for patients admitted to hospital and seen by a liaison psychiatry service with two control groups—the first is a patient group who were admitted to the same hospital in the same study period and matched on hospital inpatient and primary care data, but were not seen by the liaison psychiatry service. Because such a design could not entirely exclude confounding by indication, we will use a second matched patient group who had been admitted to a different hospital without a liaison psychiatry service in the same study period. This second group will also be matched using data from hospital and primary care records; however, they will not have been selected on the basis of whether the responsible (acute hospital) consultant had made a decision about liaison psychiatry referral.

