### Aims and objectives

This study arises from a commissioning call by the UK’s National Institute for Health Research and represents one component (Work Stream 2) of the wider project, LP-MAESTRO,^26^ which is designed to evaluate the cost-effectiveness and efficiency of liaison psychiatry service provision in the UK. The aim of the study described in this paper is to examine care pathways for the main target populations of liaison psychiatry services and estimate the outcomes and costs associated with care. Specifically, we will:

Use routinely collected NHS data to identify patients referred to specific liaison psychiatry services and matched comparison patients who were not referred, with the aim of comparing within and between hospitals the effect of referral or non-referral of patients with similar characteristics.Estimate the cost of the care pathways of patients referred to liaison psychiatry services, and the matched comparison patient groups, and the main determinants of those costs over 12 months after an index hospital episode.

We will characterise patients according to their contact with liaison psychiatry service, for example reason for referral, scheduled or urgent referral and mental health diagnosis. We will determine those patients who were referred to liaison psychiatry services from acute (general hospital) sources, and a matched sample of cases from the same sources who were not referred. We will compare outcomes for certain marker conditions (such as mental–physical comorbidity, acute behavioural disturbance, cognitive impairment/dementia) in different liaison psychiatry service configurations.

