### Data extraction

Based on the results from earlier stages of the LP MAESTRO project, we will identify at least two and up to six configurations that best represent patterns of liaison psychiatry service across England. Defining features of such configurations will include, for example, staff mix, availability of specialist teams (eg, age-related, self-harm), hours of service provided by the specialist team and source of referrals (predominantly ED, predominantly ward, specialist services and so on). We will sample purposively to obtain 2–4 services of each type (depending on availability). Data will be extracted for patients attending the hospitals with these service elements in a 1-year index period and also for patients attending hospitals identified as not having a liaison psychiatry service in the same period. Financial year 2013–2014 was selected as the index period as it represented the latest complete year for which data was available from NHS Digital at the time of study design. Numbers of accident and emergency (A&E) attendances and inpatient admissions in the index period to estimate sample size are not publicly available at hospital level. However, numbers are published by NHS Digital at trust level,^36 37^ where one trust operates one or more hospitals. These trust-level figures provide an indicative upper bound on the A&E attendances and inpatient admissions that can be expected at any hospital operated by that trust in a given year.

Relevant variables extracted for each patient from the sources will include demographic variables (eg, age, carer support, index of multiple deprivation—a measure of locality deprivation), clinical variables (eg, diagnosis, medications) and health service utilisation variables (eg, inpatient days, general practitioner (GP) appointments, major procedures). One of the novelties of our approach is the use of variables obtained from primary and secondary care settings to tackle the substantial challenge that comes from indication bias; for example, we will use variables obtained from ResearchOne to define healthcare usage in primary care for the year before referral (2013), as a way of ensuring that outcomes in the year after referral (2015) are not attributed to easily identifiable pre-existing characteristics (case complexity) that are confounded with likelihood of referral.

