### Data analysis

We will build a standard regression model to estimate the relation between healthcare utilisation and key variables capturing the configuration of liaison psychiatry services. The dependent variable in this model will therefore be the total costs of any identified healthcare utilisation derived from factors such as inpatient days, readmission rates, ED attendances and GP visits combined with reference costs. These reference costs will be valued using national sources, including the Department of Health Reference Costs^38^ and Personal Social Services Research Institute Costs for Health and Social Care.^39^ Where these are not available, local costs will be assigned. We will choose the most appropriate base year for the analysis and adjust appropriately for the effects of inflation across years. The quantum of the liaison psychiatry service provision will be captured by already collected data related to structure and process, for example, staffing levels and contact time after referral. We will adjust for referral indication bias, either by matching for covariates or by propensity scoring.

Sample size is difficult to estimate because we have so little available data on outcomes for different service types and different patient groups. Suppose we identify six main service configurations and recruit two liaison psychiatry services for each (total n=12). For less common conditions we might expect to see one referral per week per service=100 in total in the year. For more common conditions we might perhaps see one referral per day or 600–800 in the year. These numbers will allow us to estimate the costs and cost-effectiveness of liaison psychiatry services with substantially greater precision than has been achieved to date, for example, by the RAID evaluation.

The way in which components of general hospital, general mental health and liaison psychiatry services interact with each other is complex and a key part of the project will be to determine how to capture this complexity into a set of measures for inclusion in the model.

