## Ethics and dissemination

The study is funded by the National Institute of Health Research under the Health Services and Delivery Research programme (REF: 13/58/08) and is sponsored by the University of Leeds. The study is based at the Leeds Institute of Health Sciences within the University of Leeds and will use the Information Governance Toolkit (IGT) compliant infrastructure at the Leeds Institute of Clinicial Trials Research (REF: ECC0010).

To simplify the documentation provided to underpin ethics and governance processes, the study has been partitioned into distinct phases. Each phase is characterised by the use of a specific combination of data sources to construct care pathways for patients attending a particular hospital or set of hospitals. Phase 1 is characterised by the use of data from HES and ResearchOne *only* to construct care pathways for patients attending hospitals *without* a liaison psychiatry service. A summary of the ethics and governance processes undertaken for phase 1 is provided below.

As described in the Introduction section, individual patient consent will not be feasible for this study.

Phase 1 was submitted to the NHS Research Ethics Committee (North of Scotland) on 23 February 2016 (REF: 16/NS/0025). The application was reviewed in a meeting held on 10 March 2016 and received a favourable ethical opinion on 15 March 2016. Favourable ethical opinion was contingent in obtaining management permission from the hospitals whose patients were to be included in the HES data. Management permission was received for 8 of the 11 hospitals by a stated deadline (15 December 2016) and phase 1 proceeded based on the use of HES data from these eight hospitals only.

Phase 1 was also submitted to the Confidentiality Advisory Group (CAG)^43^ at the Health Research Authority on 23 February 2016 (REF: 16/CAG/0037) to determine whether the study required Section 251 support under Regulation 5 of the Health Service (Control of Patient Information) Regulations 2002.^44^ The application was reviewed in a meeting on 21 April 2016 and was deferred pending the receipt of further information in relation to the linkage process from the research team. Further information was supplied and CAG provided a decision on 19 July 2016 that Section 251 support was not required *‘*on the basis that there is no disclosure of patient identifiable data without consent’.

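### In the no-service comparison, exposure coincides with hospital, so hospital differences that patient matching does not explain are read as an effect of referral

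*Protocol article*

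**What the plan says.** Under Study design, the Protocol article sets up two control groups. The first consists of patients "admitted to the same hospital in the same study period and matched on hospital inpatient and primary care data" who were not seen by the liaison service. The authors accept that this leaves room for confounding by indication, and respond: "we will use a second matched patient group who had been admitted to a different hospital without a liaison psychiatry service". On how these patients are matched: "This second group will also be matched using data from hospital and primary care records".

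Aims and objectives gives both comparisons one interpretation: "comparing within and between hospitals the effect of referral or non-referral of patients with similar characteristics".

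Three other places bear on the point:

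- **Choice of hospitals.** For service hospitals, Data extraction says: "We will sample purposively to obtain 2–4 services of each type". For no-service hospitals, Ethics and dissemination reports that 8 of 11 gave management permission by the deadline, and "phase 1 proceeded based on the use of HES data from these eight hospitals only".
- **Variables.** Data extraction gives patient-level examples: "Relevant variables extracted for each patient from the sources will include demographic variables", followed by clinical and service-use items.
- **Adjustment.** The one confounding adjustment stated in Data analysis is: "We will adjust for referral indication bias, either by matching for covariates or by propensity scoring".

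**The concern.** The second comparison is the article's answer to the weakness of the first. It takes away the consultant's referral decision as a source of bias, but brings in another. Whether a patient had access to a liaison service is decided entirely by which hospital admitted them. Anything that applies to everyone in a hospital, such as bed pressure, usual discharge timing, local social care supply or depth of coding, moves together with exposure. Matching on patient records removes recorded differences between patients. It does not remove a difference in how two hospitals treat the same kind of patient.

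The outcomes are exposed to this. Length of stay, occupied bed days and emergency admissions all depend on local practice, and cost is built from them. The article also gives some reason to expect differences. The Introduction says hospital characteristics did not wholly account for variation in services, which suggests, without proving, that they accounted for part of it. Data sources concedes that mental health diagnoses in routine data vary in accuracy. At stake is whether a difference between the two sets of hospitals could be reported to commissioners as the effect of liaison psychiatry.

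**Working it through.** The article states no effect size, hospital variance or formal sample size for this comparison, so there is no figure to reproduce. The checks below show the structure of the problem. The hospital SD, ICC, hospital difference and control numbers are assumptions.

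**Inputs from the article.** There are 8 no-service hospitals (Ethics and dissemination). The planning scenario has 12 services, 6 configurations × 2 (Data analysis). Data extraction allows 2 to 6 configurations with 2 to 4 services each, so 2 × 2 = 4 to 6 × 4 = 24 services. One service per hospital is assumed.

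**1. Can exposure be separated from hospital?** With 12 service and 8 no-service hospitals, the 20 hospital indicators have rank 20. Adding the service/no-service indicator leaves the rank at 20. Exposure is a linear combination of the hospital indicators, so hospital fixed effects cannot separate the two, and patient matching does not address a hospital-wide difference.

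**2. What happens to a systematic difference?** Simulation with a true liaison effect of zero and an assumed hospital difference d, in patient SD units:

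| d | Seen vs same-hospital controls | Seen vs no-service controls | Not referred (service hospitals) vs no-service controls |
|---|---|---|---|
| 0 | 0.00 | 0.00 | 0.00 |
| 0.1 | 0.00 | 0.10 | 0.10 |
| 0.2 | 0.00 | 0.20 | 0.20 |

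The bias enters one-for-one in the second comparison and is absent from the first. The last column shows that patients unaffected by the service can reveal the hospital difference. The article plans no such contrast.

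**3. Chance hospital variation only.** The SD of the difference in hospital averages is s × √(1/J₁ + 1/J₀), where s is the assumed SD between hospitals in case-mix-adjusted length of stay, and J₁ and J₀ are the numbers of service and no-service hospitals.

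| J₁ v J₀ | √(1/J₁ + 1/J₀) | 95% range, s = 10% | 95% range, s = 15% |
|---|---|---|---|
| 4 v 8 | 0.612 | ±12.0% | ±18.0% |
| 12 v 8 | 0.456 | ±8.9% | ±13.4% |
| 24 v 8 | 0.408 | ±8.0% | ±12.0% |

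For 12 v 8, the SD is 4.6% at s = 10% and 6.8% at s = 15%; multiplying the unrounded values by 1.96 gives the ranges. This measures imprecision, not systematic bias, which would come on top.

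**4. Effect on a test that ignores hospital.** In units of total variance, the true variance is ICC × (1/J₁ + 1/J₀) + (1 − ICC) × (1/n₁ + 1/n₀), while a patient-level test uses 1/n₁ + 1/n₀. Take 12 v 8 hospitals and one referral per week per service, 12 × 52 = 624 seen patients, with as many controls. A nominal two-sided 5% test then has a type I error of 8.8%, 12.6%, 19.4% and 33.9% at assumed ICCs of 0.005, 0.01, 0.02 and 0.05. For one configuration of two services at one referral per day (2 × 365 = 730 per group, 2 v 8 hospitals), it is 18.0%, 27.9%, 40.5% and 57.7%.

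**5. Does any stated step deal with it?** The adjustment in Data analysis is for referral indication. Hospital-level characteristics are named as inputs to the exploratory decision model, not to this comparison. The limitations in the Discussion cover the definition of configurations, the quality of matching data and small subgroups, but not differences between the two sets of hospitals.

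**The case against.** The strongest reply is that the two control groups are meant to have different weaknesses. One holds hospital constant and may carry indication bias; the other avoids the referral decision and may carry hospital differences. Using both is a recognised strategy, and the article does not claim that the second group is unbiased. This stands. A reader might infer that confounding by indication has simply been exchanged for confounding by hospital. The document does not support that, because the same-hospital comparison is kept.

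A reader might also infer that every difference between the hospitals is counted as a liaison effect. That goes too far: case mix captured in the matched records is removed, and deprivation and carer support, which bear on discharge, are among the extracted variables. Nor does the article say that matching uses patient records alone; its variable list is given as examples.

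Hospital-level covariates or clustering could appear in a fuller protocol or analysis plan that is not shown. Data analysis also says that measures of how general hospital, mental health and liaison services interact are still to be developed for the model. These points limit the criticism but do not answer it. The control-group structure and its interpretation are fixed in the article, and the risk is not listed among its limitations.

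Finally, a difference-in-differences correction has weaknesses of its own. Hospital effects on discharge may be larger in complex patients than in those unlikely to be referred. Spillover to unseen patients is also possible: the Introduction notes that an earlier evaluation attributed much of its benefit to patients the service had not seen. Both objections stand, and they are why the correction should not be the main estimate.

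**Conclusion.** The point holds for the comparison with no-service hospitals, and only for that one. Exposure is fully nested in hospital, so a hospital difference left after matching enters the estimate in full and would be read as an effect of referral. This should be addressed before the between-hospital results are interpreted.

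The size and direction of the bias cannot be derived from the article. The range of about ±9% to ±13% rests on an assumed hospital SD of 10% to 15% and on the 12-service planning scenario. It describes chance variation and changes with the number of services (±8% to ±18% across the 4 to 24 that Data extraction allows). A reader might take it to show that a real effect of, say, 5% would be hidden or reversed. The document gives neither an expected effect nor a hospital variance, so it supports only the statement that hospital variation of this order would matter.

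**What to change.** Keep both control groups, and make these changes to the between-hospital comparison:

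1. **Negative control.** Compare service with no-service hospitals among admissions with a low predicted probability of referral, matched on the same physical-health variables as the main comparison. Define the low-probability group, and what will count as clearly non-zero, before outcomes are examined.
2. **Rule for interpretation.** If this contrast is clearly non-zero, do not interpret the between-hospital difference as a liaison effect. A result near zero is reassuring but does not exclude hospital differences confined to complex patients.
3. **Clustering.** Allow for hospital clustering in the between-hospital intervals, with a method suited to as few as eight control hospitals.
4. **Sensitivity analysis.** Report the difference-in-differences (main contrast minus negative-control contrast) as a sensitivity analysis. State that it assumes similar hospital differences in low- and high-probability patients and no spillover to unseen patients, and that it widens the interval.
5. **Limitation.** Add between-hospital confounding to the limitations in the Discussion.

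The cost appears to be analysis work and wording. Data extraction describes data on patients attending both sets of hospitals, and the same-hospital controls already require non-referred admissions. It should be confirmed that the linked extracts include enough low-probability admissions in both sets, since ResearchOne coverage was not known in advance. The interval for the between-hospital comparison will be wider, and its conclusion may have to be withheld.
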